### Interventions and study arms

This study consists of two parallel cohorts:BT Cohort (BTC): Patients will receive a cycle of bath or of mud-bath therapy once daily for 12 days in addition to their usual treatments for FS (see below). The thermal treatment cycle will include one session per day for a total of two weeks, with a break between the fifth and seventh day to prevent the onset of a thermal crisis. This protocol aligns with current practices and is endorsed by the Italian National Health Service which covers a cycle of a 12-day treatments, once a year for patients with rheumatic diseases such as FS. The mineral thermal baths will be carried out in a single tub or in a pool, with a duration of 10 min at a temperature of 37–38° C. The thermal mud will be applied to the skin according to standardized methods, with a duration of 15–20 min, at temperatures ranging between 40–45° C. A rest period of about 20–30 min will follow BT treatment. The whole treatment duration will last 1 h, approximately. Only muds and baths belonging to the classes of sulfurous, bicarbonate, chloride-sodium, sulphate and arsenical-ferruginous waters—according to the classification of Marotta and Sica (1933), will be allowed.Control Cohort (SCC): This group will include patients who will refuse the BT for personal reasons. Patients will continue their established routinely care for FS.

The usual care treatment will correspond to pharmacological and non-pharmacological therapies as reported in EULAR guidelines (Macfarlane et al. 2016). The intervention program must have already been stabilized for at least 3 months before the start of the study. During the study period, the patient can modify the therapy if necessary; this change will be reported.

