### Sample size

The primary outcome is the modification of the FIQ total score, whose minimum clinically relevant difference is 14% as compared to its initial value (Burckhardt et al. 1991). We expect a decrease in the FIQ total score of at least 14% in the 30% of the control cohort and 45% in the BT cohort. A number of 217 patients per group allows estimating an absolute difference of 15% (45—30%) in the incidence of the primary outcome between the two cohorts at an alpha level = 0.05 and with a power of 90% (Pearson’s chi-squared test). Assuming a loss to follow-up of 20%, 260 (217 + 43) patients will be enrolled per group, for a total of 520 patients.

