### Statistical analysis plan

#### Primary outcome

The primary outcome of the study will be the difference in the proportion of patients with reduction in FIQ-Total score > 14% in the BT vs. the control cohort. As described above, Pearson’s chi-square test will be used to evaluate the statistical significance of this difference, considered clinically relevant if ≥ 15%, at an alpha = 0.05 level and with a power of 90%. Subsequently, a binomial regression model (BRM) will be used to quantify the size of this difference and its precision (95% confidence interval) (Long and Freese 2006). The response variable of the BRM will be the proportion of subjects with a reduction in the FIQ-Total score > 14% at 15 days, and the predictor will be the cohort (discrete: 0 = control cohort; 1 = BT cohort). The effect size estimated by the BRM will be expressed both as absolute and relative risk change. Marginal estimates with 95% confidence intervals of the percentages of patients with reduction in FIQ-Total score > 14% in the two cohorts will be calculated.

In the BT cohort, we will also use a BRM having as a response variable, the proportion of subjects with a reduction in the FIQ-Total score > 14% and time as predictor (discrete; 0 = 15 days; 1 = 45 days) to verify the stability of the change in the FIQ-Total score at 30 days. A Bonferroni correction will be used to correct the 95% confidence intervals and associated p-values. The univariable BRM described above for the evaluation of the primary outcome between the BT and control cohorts will subsequently be expanded to a multivariable model by adding predictors (= potential confounders) determined preliminarily with the clinicians participating in the study. An univariable selection of the predictors will not be made, but they will be progressively added to the model to verify the effect on the relative risk estimated by the model itself (Greenland and Pearce 2015). Interactions initially determined or suggested by the multivariable analysis may also be included among the predictors. It is possible, and indeed expected, that the BRM will have to be replaced by a Poisson regression model (PRM) with robust confidence intervals, to overcome the well-known problems of fitting a BRM with multiple predictors (Zou 2004; Lumley et al. 2006). At this stage, we will only model the relative risk because, being this a cohort study, the relative risk measure is expected to be more transferable than the absolute risk.

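### The confounder-adjusted analysis is limited to the relative risk, so no adjusted risk difference with a confidence interval is planned, although the primary outcome and its 15-point criterion are absolute

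*Protocol article*

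**What the plan says.** Three parts of the protocol article put the question on the absolute scale.

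- The section on the primary outcome, within the statistical analysis plan, sets the target measure as follows: "The primary outcome of the study will be the difference in the proportion of patients with reduction in FIQ-Total score > 14" per cent, BT against control. An unadjusted Pearson chi-square test is applied to this difference, which is "considered clinically relevant if ≥ 15%, at an alpha = 0.05 level and with a power of 90" per cent.
- Sample size: responders are expected "in the 30% of the control cohort and 45% in the BT cohort", and "A number of 217 patients per group allows estimating an absolute difference of 15" percentage points.
- Interventions and study arms, on the control cohort: "This group will include patients who will refuse the BT for personal reasons". The cohorts are thus formed by patient choice.

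The estimation plan has two steps. A binomial regression with cohort as its only predictor gives the effect as both an absolute and a relative change, with marginal percentages and confidence intervals for each cohort. Potential confounders, agreed beforehand with the clinicians, are then added step by step, and interactions may be included. The authors expect to need a Poisson model with robust intervals at this point. Of this second step they say: "At this stage, we will only model the relative risk because, being this a cohort study", and give as the reason that the relative risk should transfer better to other settings.

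**The concern.** The scale changes where adjustment begins. The measure that defines the primary outcome, drives the sample size and carries the relevance criterion is planned only from the model without confounders. Once confounders enter, that measure is dropped.

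This matters because the controls are refusers. People who decline a spa course for personal reasons may differ from those who accept in ways that predict response, such as expectation, severity, work or travel. The one planned figure that can be set directly against 15 points, with its uncertainty, is the one most exposed to those differences. The adjusted figure is on another scale.

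The plan does not do this for its other endpoints. For the secondary scores, the Secondary outcomes section adds confounders and follows their effect on the difference in scores, which is the scale on which those outcomes are defined.

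**Working it through.** **Step 1: confirm the scale of the design.** Inputs from Sample size: p0 = 0.30, p1 = 0.45, alpha 0.05 (taken as two-sided, since the sidedness is not stated), power 90%, Pearson chi-square without continuity correction. The mean proportion is 0.375.

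n = [1.960 × √(2 × 0.375 × 0.625) + 1.282 × √(0.30 × 0.70 + 0.45 × 0.55)]² / 0.15²

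= [1.960 × 0.6847 + 1.282 × 0.6764]² / 0.0225 = 216.8, rounded up to 217 per group.

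The stated 217 reproduces, with power 90.0%. At that size the 95% interval for a 15-point difference has half-width 1.96 × √(0.4575 / 217) = 0.090, or about 9 points.

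**Step 2: what a relative risk says about 15 points.** Difference = p0 × (RR − 1). The planning relative risk is 0.45 / 0.30 = 1.5. The control risks below, other than the planned 30%, are assumptions.

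| Control risk | Difference at RR 1.5 | RR needed for 15 points |
|---|---|---|
| 20% | 10 points | 1.75 |
| 25% | 12.5 points | 1.60 |
| 30% | 15 points | 1.50 |
| 35% | 17.5 points | 1.43 |
| 40% | 20 points | 1.375 |

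An adjusted relative risk therefore needs a control risk before it can be read against the criterion.

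**Step 3: how far crude and adjusted differences can part (assumed illustration).** One binary prognostic factor splits patients into two strata, with control response 20% and 40%. The relative risk is 1.25 in both, so BT response is 25% and 50%. The better stratum makes up 50% of controls and 80% of the BT cohort.

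- Crude control: 0.5 × 20% + 0.5 × 40% = 30%.
- Crude BT: 0.2 × 25% + 0.8 × 50% = 45%.
- Crude difference: 15 points. Crude RR: 1.5. The criterion is met exactly.
- Standardised over both cohorts (equal size, so 65% in the better stratum): control risk 0.35 × 20% + 0.65 × 40% = 33%; difference 33% × 0.25 = 8.25 points. The criterion is not met.

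**Step 4: what the plan would print in that case.** It would give a crude difference of 15 points with an interval, a crude RR of 1.5 and an adjusted RR of 1.25. It would not give the 8.25 points or an interval for it.

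**The case against.** The strongest reply is that confounding is handled and the reader can see its effect. The same responder endpoint is adjusted, only on the relative scale. The cohort-only model also reports a relative risk, so crude and adjusted values stand side by side; in the example, a fall from 1.5 to 1.25 shows at once that the crude result was inflated. The control risk will be observed as well. With a log-link model and no cohort interactions, 30% × (1.25 − 1) = 7.5 points, which is the adjusted difference for the control population. Like the 8.25 points for both cohorts together, it is clearly below 15.

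All of that stands. A reader might infer that the primary outcome is never adjusted, or that crude and adjusted results could conflict with no means of resolving them. The article supports neither reading. Nor does Step 2 mean that the control risk will be unknown, since marginal percentages for both cohorts are planned.

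Two further replies also carry weight. The 15-point figure is attached to the chi-square comparison, and nothing says that success is decided by the multivariable model. Transferability is a reasonable ground for reporting a relative risk.

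What remains is narrower. The conversion is left to the reader and has no interval. It also has no single answer once cohort interactions are included, because there is then no one relative risk to insert. Transferability supports adding the relative risk, but not leaving out the measure that defines the outcome. The gap cannot be put down to the brevity of an article, because the text states the restriction outright.

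**Conclusion.** The point holds in this limited form: the only planned absolute difference with a confidence interval is unadjusted and comes from self-selected cohorts, while the outcome, the sample size and the relevance criterion are all absolute. The weakness lies in what the adjusted analysis is set to report. The model itself is sound.

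The size depends on how strongly the cohorts differ. In the assumed example the crude difference is 15 points and the standardised one 8.25. If the better stratum were equally common in both cohorts (50%), crude and standardised differences would both be 7.5 points. The documents do not give the figures needed to say where the study will fall.

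A reader might also infer that the adjusted difference should replace the chi-square comparison as the primary analysis. That does not follow from this point. Whether an unadjusted primary test suits self-selected cohorts is a separate question. Nor would the adjusted difference be free of confounding: it accounts only for the confounders that are measured and modelled.

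**What to change.** In Statistical analysis plan, Primary outcome:

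- Delete the restriction of the multivariable stage to the relative risk.
- Prespecify a standardised (marginal) risk difference from the same multivariable binomial or robust Poisson model. Predict each patient's risk with cohort set to BT and then to control, average each over a named population, and subtract. Name the population: in the example the answer is 7.5 points over controls and 8.25 over both cohorts.
- Give its 95% confidence interval by the delta method, pooled over the imputed datasets where multiple imputation is used.
- State which model supplies it, since predictors are added progressively. The model with the full set of confounders agreed beforehand is the natural choice.
- Report it beside the adjusted relative risk, and read the 15-point criterion against the adjusted difference as well as the crude one.

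The same averaging gives one summary if interactions are included.

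The cost is a change of wording and modest analysis work. It is somewhat more than a single command when at least 100 imputed datasets have to be pooled, but no further data are needed. The adjusted difference may turn out smaller or less precise than the crude one.

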#### Secondary outcomes

The secondary outcomes of the study will be the differences in VAS, SF-12, STAI, and CES-D between the BT and control cohorts. These differences will be evaluated using a random effects linear regression model (RE-LRM) (Rabe-Hesketh and Skrondal 2021) 39. The response variable of such models will be the (continuous) score obtained from the scale and the predictors will be: 1) time (discrete; 0 = baseline; 1 = 15 days), 2) the cohort (discrete; 0 = control cohort and 1 = BT cohort), and 3) a time*cohort (discrete*discrete) interaction, with the random effect assigned to the patient. A Bonferroni correction will be used to correct the 95% confidence intervals and associated p-values. As already described for the BRM used for the evaluation of the primary outcome, also the RE-LRM will be expanded to a multivariable model by adding predictors (= potential confounders) determined preliminarily with the clinicians participating in the study. Interactions initially determined or suggested by the multivariable analysis may also be included among the predictors. An univariable selection of the predictors will not be carried out, but predictors will be progressively added to the model to verify the effect on the estimate of the difference in the scores for the BT and control cohort (Greenland and Pearce 2015).

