## Abstract

Balneotherapy (BT) is considered an effective, non-pharmacological approach, in the multimodal treatment of the Primary Fibromyalgia Syndrome (FS). However, the evidence of efficacy and tolerability of BT in FS is still limited. This is a prospective multi-center two-cohort observational study. The main aim will be the comparison of the Minimal Clinically Important Difference (according to Fibromyalgia Impact Questionnaire—FIQ) achievement in FS patients treated with BT vs standard care. Secondary objectives will be to assess: a) BT impact on pain, quality of life, anxiety and depression; b) the persistence of benefits in six weeks c) BT safety profile. All FS patients with a stable treatment in the past 3 months and a moderate to severe disease (FIQ score ≥ 39) will be enrolled after providing written informed consent. Patients will be divided into two Cohort: a) BT Cohort (i.e., BT in addition to standard care)—BTC; b) Control Cohort (i.e., only standard care)—SCC. There will be three assessments: baseline, two and six weeks (i.e., one month after BT end in BTC). At each of them the subject will fill in the following questionnaires: FIQ, VAS pain, Short Form Health Survey 16, State-Trait Anxiety Inventory and Center for Epidemiological Studies Depression Scale. We expect to observe a more relevant improvement of disease activity in BTC than in SCC. The positive effect may extend even to pain, quality of life, anxiety and depression. The short- and medium-term effects are likely to be similar, without any significant warning in terms of tolerability. Collected data, deriving from a large sample of patients, will provide a new insight of BT role in moderate to severe FS treatment. In particular, it will be possible to quantify the short and medium-term BT impact on disease activity and secondary symptoms related to FS.

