The primary aim of this study will be to evaluate whether BT increases the proportion of patients achieving the Minimal Clinically Important Difference (MCID) as measured by the Fibromyalgia Impact Questionnaire (FIQ), compared to standard care. Secondary aims will be a) the assessment of BT additional effects on pain, quality of life, anxiety and depression, b) the persistence of clinical efficacy over a six-week follow-up, c) the tolerability of BT by recording all adverse events, their severity and possible relationship with the therapy.

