#### Secondary outcomes

##### Pain

Pain intensity will be evaluated by a Visual Analogue Scale (VAS), a 10-cm long line with the value 0 on the left indicating “no pain” and the value 10 on the right indicating the “worst imaginable pain” (Scott and Huskisson 1976).

Furthermore, we will consider as a secondary outcome, the Widespread Pain Index (WPI) that is a measure of the number of painful areas (score range = 0–19) on the patient’s body over the last week before the assessment (Wolfe et al. 2010).

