### Follow up

Following enrollment, each patient will be examined for 3 consecutive times; at baseline (T0), after 2 weeks (T1), and after 45 days (T2) (one month after the end of the cycle of the therapy for the BT Cohort) (Fig. 1). T0 and T1 visits will be carried out by the physician in the enrollment setting. The T2 visit will be carried-out by phone. The study will be considered concluded when all follow-up data for each patient will be collected.

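### Day-45 data are collected in both cohorts but enter no comparison with control: the secondary models stop at day 15, day-45 FIQ response is modelled only within the BT cohort, and WPI is not in the analysed list

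*Protocol article*

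**What the plan says.** The aims at the end of the Introduction include, as secondary aim b, "the persistence of clinical efficacy over a six-week follow-up". The Abstract goes further and says that "it will be possible to quantify the short and medium-term BT impact on disease activity and secondary symptoms related to FS".

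Under Follow up, with no distinction by cohort, "each patient will be examined for 3 consecutive times; at baseline (T0), after 2 weeks (T1), and after 45 days (T2"; the last visit is by telephone. The Abstract adds that "At each of them the subject will fill in the following questionnaires", and lists FIQ, pain VAS, the short-form health survey, STAI and CES-D.

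In the Statistical analysis plan, the between-cohort FIQ model is fixed at 15 days. Day 45 appears once, in a model introduced by "In the BT cohort, we will also use a BRM", where time (15 or 45 days) is the predictor and the purpose is to check that the change is stable. The random-effects linear model for the secondary outcomes has a patient random effect, cohort, a time-by-cohort interaction, and "time (discrete; 0 = baseline; 1 = 15 days". Its response variables are VAS, SF-12, STAI and CES-D.

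Under Pain in the outcomes section, however, "we will consider as a secondary outcome, the Widespread Pain Index (WPI", and WPI is also in Table 1.

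**The concern.** The time codes, the cohort used for the day-45 model and the list of responses are explicit choices. They are not details left to a fuller document, and an analyst who follows them will set aside the whole third visit for every secondary scale and all control FIQ data at that visit.

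The stated hypothesis is comparative: BT added to standard treatment is better than standard treatment alone. After day 15 the plan contains no comparison with standard care. It could report that BT responders at day 15 were still responders at day 45, but not whether BT patients were still better off than controls by then. For VAS, SF-12, STAI and CES-D it could report nothing about day 45, with or without a control.

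**Working it through.** **Step 1. Collected against analysed.** From the Abstract, Follow up, Pain, and the two outcome subsections of the Statistical analysis plan:

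| Outcome | Day-45 collection | BT vs control, day 15 | BT vs control, day 45 | Other use of day 45 |
|---|---|---|---|---|
| FIQ response | both cohorts | yes | none | 15 vs 45 days, BT only |
| VAS, SF-12, STAI, CES-D | both cohorts | yes | none | none |
| WPI | visits not stated | not listed | not listed | none |

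With 260 patients planned per cohort, up to 520 day-45 assessments are kept out of the secondary models. Up to 260 control FIQ scores at day 45 are unused, or 260 × 0.8 = 208 if the assumed 20% loss applies at that visit.

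**Step 2. The plan's own figure.** Inputs from Sample size: 30% control, 45% BT, alpha 0.05 (two-sided assumed, as sidedness is not stated), power 90%. With pooled variance and no continuity correction:

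n = [z(0.975)·√(2·p̄·(1−p̄)) + z(0.90)·√(p1(1−p1) + p2(1−p2))]² / (p2−p1)²

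p̄ = 0.375, so 2 × 0.375 × 0.625 = 0.46875, root 0.6847. 0.30 × 0.70 + 0.45 × 0.55 = 0.4575, root 0.6764.

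n = (1.960 × 0.6847 + 1.2816 × 0.6764)² / 0.15² = 2.2087² / 0.0225 = 216.8, that is 217 per group.

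The stated 217 reproduces. It is a calculation for the day-15 contrast only.

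**Step 3. What the BT-only model can tell.** The article gives no day-45 rates, so these are assumptions. Hold BT response at 45% at both visits and let control at day 45 range from 30% to 45%. The BT-only model estimates 45 − 45 = 0 points of change in every row. Power for a two-sided 0.05 test between cohorts, without Bonferroni or confounder adjustment, is Φ{[d√n − 1.960·√(2p̄(1−p̄))] / √(p1(1−p1) + p2(1−p2))}.

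| Control, day 45 | BT-only estimate | BT − control, day 45 | Power, n = 217 | Power, n = 208 |
|---|---|---|---|---|
| 30% | 0 | 15 points | 0.90 | 0.89 |
| 35% | 0 | 10 points | 0.57 | 0.55 |
| 40% | 0 | 5 points | 0.18 | 0.18 |
| 45% | 0 | 0 points | 0.025* | 0.025* |

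*Chance of a false rejection in favour of BT.

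The planned model returns the same answer in all four rows, although the advantage over standard care runs from fully kept to gone. A non-significant change between days 15 and 45 would not demonstrate stability either.

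**The case against.** Aim b names no comparator. The plan pairs a controlled contrast at day 15 with a within-BT check that the response is maintained, and this is a legitimate reading of persistence. This stands: a reader might infer that the persistence aim has no analysis at all, and for FIQ response that is not so. It does not help the other four scales, for which the Abstract promises a medium-term effect and no day-45 model exists.

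A reader might also infer that 45% persisting in BT would overstate the BT effect threefold (45 against 15 points) if control held at 30%. The article does not support that. The stability model estimates a change, here zero, and nobody attributes the full 45% to BT. With control steady at 30% the difference is 15 points at both visits, so concluding that the effect lasts would be right. The damaging case is control catching up.

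Regression to the mean after entry at FIQ 39 or more is a weaker argument than it looks. Both visits are measured against the same baseline, so much of that shift would already be present at day 15. Any later drift is not quantified.

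The absence of a continuous FIQ model contradicts nothing, because the article's FIQ outcome is a responder proportion. Nor can one say that day-45 WPI is available: the Abstract's list of questionnaires leaves WPI out, and no visit schedule is given for it.

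Two practical objections also stand. Visit T2 is by telephone, while VAS is a 10-cm line and FIQ, STAI and CES-D are self-administered, so change from day 15 to day 45 mixes modes. More contrasts also enlarge a Bonferroni family whose size the article does not give.

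**Conclusion.** The point holds for what the article fixes explicitly. No day-45 value of VAS, SF-12, STAI or CES-D enters any described analysis. Day-45 FIQ response is examined only within BT, which shows within-cohort stability but leaves an advantage over control anywhere from 15 to 0 points undetermined under the illustrative rates. WPI is declared as an outcome and then omitted from the analysed list.

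This is a mismatch between secondary aims and secondary models that should be corrected before analysis. It does not touch the primary result: the day-15 responder comparison and its sample size of 217 per group stand as planned. The size of any resulting error cannot be calculated, since the article gives no day-45 rates; the 30% to 45% range for control is an assumption.

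**What to change.** 1. In the random-effects linear model, code time as 0, 15 and 45 days, keep the time-by-cohort interaction, and report the cohort contrast at day 15 and at day 45.
2. Model FIQ response at days 15 and 45 in both cohorts with a cohort-by-time interaction, allowing for two measurements per patient. Use BT versus control at day 45 as the persistence estimate and keep the within-BT change as description. Because controls are patients who decline BT, apply the confounder adjustment already planned for day 15.
3. Add WPI to the response variables at the visits where it is collected, and state those visits.
4. Because T2 is by telephone in both cohorts, prefer the between-cohort contrast at day 45, where the mode is the same, to within-cohort change.
5. State the Bonferroni family.

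Cost: wording, with no new visits for the scales already scheduled at T2. The multiplicity price is real. If the family is taken as six scores (VAS, two SF-12 components, two STAI scales, CES-D; an assumption), the threshold is 0.05/6 = 0.0083. With day 45 it is 0.05/12 = 0.0042, and with WPI at both visits 0.05/14 = 0.0036. Power at day 45 will also be low if the difference has shrunk, so the estimate and its interval should be reported, not only the test.

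### Adding baseline confounders as main effects to the secondary mixed models cannot change the time-by-cohort estimate, so the planned adjustment does not address confounding of two-week change

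*Protocol article*

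**What the plan says.** The Secondary outcomes part of the protocol article's Statistical analysis plan models each continuous score with a random-effects linear regression. The predictors are "time (discrete; 0 = baseline; 1 = 15 days"), cohort, and "a time*cohort (discrete*discrete) interaction, with the random effect assigned to the patient".

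The adjustment is described as a carry-over from the primary binomial model: "also the RE-LRM will be expanded to a multivariable model by adding predictors (= potential confounders) determined preliminarily with the clinicians". It is judged by stepwise inclusion: "predictors will be progressively added to the model to verify the effect on the estimate of the difference in the scores". The same paragraph adds: "Interactions initially determined or suggested by the multivariable analysis may also be included among the predictors". It names no confounder-by-time interaction, and it does not say which coefficient or contrast is the difference in scores being monitored.

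Interventions and study arms describes the control cohort: "This group will include patients who will refuse the BT for personal reasons".

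**The concern.** Patients who decline balneotherapy (BT) may differ from those who accept it in ways that predict how their scores move over two weeks, such as treatment expectation or baseline severity. The multivariable step is where the plan deals with measured confounding. In the primary model the response is already a change (a FIQ reduction above 14%), so a covariate main effect adjusts it. In the secondary models the response is the score at each visit, and the change contrast sits in the interaction. A baseline covariate added beside that interaction adjusts the level of the score, not its change.

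Two things are at stake. Change that belongs to a confounder may be credited to BT, or may mask a BT effect, depending on its direction. And the add-and-see check can show a stable estimate whether or not there is confounding.

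**Working it through.** **Algebra.** The stated model for patient i at visit t (0 or 1) is

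score = b0 + b1·t + b2·cohort + b3·t·cohort + u_i + e_it.

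With both visits present and a patient random intercept, the estimate of b3 is the BT-minus-control difference in mean change. Add a baseline covariate X as a main effect, g·X_i. The change for patient i is then

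(b0 + b1 + b2·cohort + b3·cohort + g·X_i) − (b0 + b2·cohort + g·X_i) = b1 + b3·cohort, plus error.

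X has dropped out, so b3 is estimated from the same changes as before. If X·t is added with coefficient h, the change becomes b1 + b3·cohort + h·X_i, and b3 is adjusted. With complete pairs this is the same as regressing change on cohort and X.

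**Numerical check of the invariance.** Assumed inputs: 520 patients, true BT effect 0, X predicting cohort (log-odds 1 per SD), level slope 0.5 and change slope −0.6 per SD, 60 datasets. Since X affects the baseline score by 0.5 per SD and the baseline cohort difference averaged 0.401, the cohorts differ by about 0.401 / 0.5 = 0.80 SD in X. The expected bias in b3 is −0.6 × 0.80 = −0.48. The confounder is deliberately strong, because the purpose is to test the algebra. Mean b3:

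| Data | No X | X as main effect | X and X·time | Largest move from adding X |
|---|---|---|---|---|
| Complete | −0.479 | −0.479 | 0.018 | 1.8e-14 |
| 20% random loss, not imputed | −0.4885 | −0.4880 | 0.005 | 0.008 |
| About 20% loss depending on X, not imputed | −0.463 | −0.458 | 0.005 | 0.016 |

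The complete-data standard error was 0.134 with or without X. The identity also holds inside each dataset completed by multiple imputation, because both visits are then filled.

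**If the 15-day difference (b2 + b3) is read instead.** It does move, from −0.078 to −0.234 in the complete data, a shift of −0.156. The cohort coefficient moved from 0.401 to 0.245, also −0.156. So the whole shift comes through b2, and here it went further from the true value of 0. With X·time in the model the 15-day difference was 0.014.

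**Possible size.** The article gives no confounder strengths, so these are assumptions: X differs by d SD between cohorts and shifts change by 0.3 residual SDs of change per SD of X; no BT effect. The number per cohort is 260 × 0.8 = 208, from the planned enrolment and 20% loss. In residual-SD units the total SD of change is √(1 + 0.3²) = 1.044, and the standard error of the difference is 1.044 × √(2/208) = 0.1024. The standardised bias is 0.3d / 0.1024.

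| d | Standardised bias | Rate at 5%: normal approx. / simulated | Rate at 0.0125: normal approx. / simulated |
|---|---|---|---|
| 0.2 | 0.06 / 0.1024 = 0.59 | 9.0% / 9.2% | 2.9% / 2.8% |
| 0.3 | 0.09 / 0.1024 = 0.88 | 14.2% / 13.9% | 5.3% / 5.0% |
| 0.5 | 0.15 / 0.1024 = 1.46 | 31.1% / 31.1% | 15.1% / 14.9% |

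The simulated figures use 8000 runs per setting. With X·time the simulated rates were 4.9% to 5.2% at 5% and about 1.3% at 0.0125. With a slope of 0.2 the main-effect rates at 5% were 7.0%, 9.2% and 17.1%. The 0.0125 level assumes four tests (0.05 / 4).

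**The case against.** Several points on the other side stand and limit the concern.

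- **Interactions are permitted.** A confounder-by-time term could be fixed in advance or added later under the existing wording. A reader might infer that the plan rules out proper adjustment; it does not. But the term is optional, and it is not identified as the one that does the adjusting.
- **The estimate is not named.** The article never says that the monitored difference is the interaction coefficient. If it is the 15-day difference, the check would show movement, so it is too strong to say that the check can never respond. That movement reflects level, not change, and does not give a properly adjusted effect.
- **Predictors need not be time-constant.** Therapy changes are recorded ("During the study period, the patient can modify the therapy if necessary; this change will be reported"). A visit-level covariate does move the interaction, from −0.630 to −0.478 in a simulated example. Such changes occur after cohort entry, however, and do not stand in for baseline confounders.
- **The model already gives some protection.** The time-by-cohort contrast removes stable differences in level, measured or not. One might infer that the multivariable step is the only safeguard; it is not. What remains is confounding of change.
- **The error rates are illustrative.** They rest on assumed strengths. The plan prescribes a Bonferroni correction, so the 5% column overstates the rates under that correction, and more than four tests would lower them further.

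Nor does the article say that an unmoved estimate will be reported as proof of robustness. The point is only that it could not serve as such. This is also more than detail left to a fuller plan: the method is stated, and for baseline confounders it does not do the job given to it.

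**Conclusion.** The concern holds in limited form. For baseline confounders entered as main effects, the secondary models leave the time-by-cohort estimate exactly unchanged with complete or imputed pairs, and nearly unchanged with about 20% loss. That result does not depend on assumed effect sizes. The stated step therefore does not address confounding of two-week change in VAS, SF-12, STAI or CES-D, and stability of that estimate under it carries no information.

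How much this matters in the trial is unknown, in size and in direction. Under the assumed confounders with slope 0.3, the false-positive rate runs from about 9% to 31% at a nominal 5%, and from about 3% to 15% at an assumed alpha of 0.0125. The primary binomial or Poisson model has one change-based response per patient and is not affected. The change is worth making before analysis, but it concerns secondary outcomes only.

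**What to change.** In the Secondary outcomes part of the analysis plan:

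1. Name the time-by-cohort coefficient as the effect estimate for each score.
2. Replace the adjustment wording with: each prespecified baseline confounder is entered together with its interaction with time. Equivalently for complete pairs, regress the 15-day change on cohort and the confounders.
3. Report the adjusted effect, with its corrected 95% confidence interval, from the model holding all of these terms.
4. Do not use movement of the estimate after adding main effects alone as a check on confounding.

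No new data are needed. The cost is one extra parameter per confounder and a negligible change in precision: in fitted examples the standard error went from about 0.200 to 0.201 and from 0.204 to 0.207, and in the 520-patient simulation from 0.1337 to 0.1362.
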